#### 3.3.1 Structural MRI

Two structural images are collected for each participant: a multi-echo T1-weighted structural image with 0.8 mm isotropic voxels, TR 2,500 ms, TEs 1.81 ms, 3.60 ms, 5.39 ms, 7.18 ms, TI 1,000 ms, FOV 256 mm, flip angle 8 degrees, GRAPPA acceleration factor 2, and a T2-weighted structural image with 0.8 mm isotropic voxels, TR 3,200 ms, TE 564 ms, FOV 256 mm, and GRAPPA acceleration factor 2.

#### 3.3.2 Resting state functional MRI

A total of 18 min of resting state fMRI data is collected, divided into two ~9-min, 300-volume scans with opposite phase encoding (anterior-posterior and posterior-anterior) but otherwise identical sequence parameters. Resting state fMRI is collected with a multi-echo, multi-band BOLD sequence with 2.5 mm isotropic voxels, TR 1,670 ms, TEs 15.60 ms, 38.20 ms, 60.80 ms, 83.40 ms, GRAPPA acceleration factor 2, multiband factor 4, echo spacing 0.50 ms. During the resting state fMRI scan, participants are asked to remain awake, look at a white crosshair presented on a black screen, and to think about nothing in particular. Active noise cancellation during resting state is done using OptoAcoustic noise canceling headphones (Optoacoustics Ltd, Mazor Israel).

#### 3.3.3 Functional MRI tasks

Two reward-based fMRI tasks are utilized for this study: the Apple Gathering Task and Card Guessing Task. For both tasks, fMRI is collected using a multi-band BOLD sequence with 2.0 mm isotropic voxels, TR 1,300 ms, TE 22.80 ms, multiband factor 3, FOV 208 mm, flip angle 64 degrees, echo spacing 0.53 degrees, GRAPPA acceleration factor 2. For each task, an additional brief (< 1 min) scan is collected prior to the task scan with identical sequence parameters but with opposite phase encoding. Active noise cancellation during functional MRI tasks is done using OptoAcoustic noise canceling headphones (Optoacoustics Ltd, Mazor Israel).

##### 3.3.3.1 Apple Gathering Task

The Apple Gathering Task (AGT) (Bonnelle et al., 2016; Armbruster-Genç et al., 2022) is an effort- and reward-based decision-making task. Participants are informed that they will receive an extra monetary reward based on their performance on this task; this reward ranges from $12 to $24. Participants are presented with a screen showing an apple tree with a variable number of apples (3, 6, 9, or 12). The apple tree is accompanied by a horizontal line across the tree trunk; the height of this line indicates the amount of effort that would be required to collect the apples on that tree (low, med-low, med-high, high), calibrated to each participant's personal maximum hand grip strength for each hand. Effort is expended by participants squeezing a hand-grip measurement tool (i.e., two dynamometers from Biopac Systems, Inc. using the MP160 and two DA100C amplifiers); this sends a signal to the screen, which then shows a vertical bar indicating the amount of effort they are expending. If participants successfully squeeze the hand grip above the required effort threshold for at least 2 s, they win all of the apples on the tree. If they do not successfully squeeze the hand grip, they do not win any apples that round. At the beginning of each trial, an apple tree is presented with a quantity of apples and required effort level; participants are then asked yes/no if they want to accept the trial or decline it. Upon acceptance of most trials, the apple tree will appear on either the left or the right side of the screen (counterbalanced), and participants will squeeze the grip measurement tool on the side where the tree appears to try to make their effort bar reach the horizontal line. In 25% of trials that are accepted, the participant does not need to squeeze the hand grip and instead simply acquires the apples. If the participant declines a trial, they move on to the next trial in which a new number of apples and amount of effort are offered. The task involves 80 trials in a 4 (Apples: 3, 6, 9, 12) × 4 (Effort: low, med-low, med-high, high) design with 5 trials for each of the 16 levels; each trial lasts 12 s. This task lasts up to 26 min in total, depending on the number of trials that the participant accepts. The AGT was originally administered during fMRI, but is now being collected as an outside-scanner task due to funding changes. Participants are informed of the monetary reward amount they will receive at the end of the scan (or at the end of the task, for those completing it outside of the scanner). The behavioral dependent variable is the participant's propensity to accept trials based on the number of apples and amount of effort. The primary neural dependent variables are reward anticipation (i.e., neural response when thinking about whether to accept or decline a trial) and response to reward attainment (i.e., neural response upon successfully obtaining apples).

##### 3.3.3.2 Card Guessing Task

The Card Guessing Task (CGT) (Forbes et al., 2009) is a reward-based task in which participants are informed that they will receive monetary reward for their performance on the task; however, the task is designed such that participants will have the same number of wins, losses, and neutral outcomes regardless of the choices they make, resulting in each participant receiving the same monetary reward. Participants are debriefed on this design at the end of their study participation. Prior to beginning the task, participants are told that the compensation will be as follows: +$6 for each win, -$2.50 for each loss, and no addition or deduction for neutral outcomes. Participants first have 3 s to guess whether the next randomly chosen card will be higher or lower than 5. If they do not guess within 3 s, the task skips to the next trial. Once a guess is submitted, it is briefly presented on the screen. Then, the participant is shown a screen revealing trial type; the three trial types are gain (win if correct, neutral if incorrect), loss (loss if incorrect, neutral if correct), and gain/loss (win if correct, loss if incorrect). Then, some number from 1 to 9 (excluding 5) is presented on the screen; this number is not fully random, but rather randomized within whatever range would align with the predetermined outcome for that trial based on the participant's guess. For example, if the predetermined outcome was for the guess to be correct, and the participant selected “high”, the screen would present some number from 6 to 9. Finally, the predetermined outcome feedback is presented, informing the participant if the outcome was a win (green up arrow and dollar sign to indicate gaining reward), loss (red down arrow and dollar sign with an “X” through it to indicate losing reward), or neutral (a yellow circle). The duration of each screen varies from trial to trial; the average trial duration across the task is 13 s. There are 36 trials, for a total task duration of ~8 min. There are no reward-based behavioral dependent variables in this task, as the only behavioral measure is the percentage of trials participants guess on, in which a low percentage would indicate inattention to the task. The main neural dependent variables are reward/loss anticipation and attainment of gains, losses, or neutral outcomes.

#### 3.3.4 Magnetic resonance spectroscopy

Proton magnetic resonance spectroscopy (MRS) data is acquired using the HERMES sequence (TR: 2,000 ms; TE: 80 ms; 320 averages) (Chan et al., 2016; Saleh et al., 2016). This includes a full spectrum of brain metabolites as well as edited spectra for gamma-aminobutyric acid and glutathione quantification. A 2.5 × 2.5 × 3 cm voxel is placed on the midline of the brain in the prefrontal cortex and rotated to cover the dorsal anterior cingulate cortex and the dorsomedial prefrontal cortex (Figure 2). Siemens automatic shimming is used, with manual shimming if necessary, to achieve a displayed full-width half-max value of < 17 Hz for the unsuppressed water peak. Previous literature has demonstrated that at least in some regions of the brain, LIFUP is capable of altering metabolites as measured by MRS, though that study investigated the regions being stimulated rather than downstream regions (Yaakub et al., 2023). The placement of this voxel was chosen given literature suggesting alterations in an array of metabolites in the prefrontal cortex and anterior cingulate cortex of patients with depression (Xie et al., 2023). We anticipate that LIFUP to the caudate and nucleus accumbens may be able to alter metabolites in these regions due to the well-documented connections between the striatum and the anterior cingulate and medial prefrontal cortices as part of reward processing pathways (Haber, 2011).

**Figure 2 F2:**
[figure not shown]
MRS voxel placement. The typical location and orientation of the MRS voxel overlaid on the MNI152 brain template.

#### 3.3.5 Field maps

For each functional MRI sequence, a pair of spin echo-based EPI images is collected with opposite phase encoding to each other, but matched along the axis of the phase encoding for the functional data and with identical voxel size to the corresponding sequence; this pair of images can be processed to create field maps to use for fMRI distortion correction.

### 3.4 Digital phenotyping

Participants in this study will wear an Apple Watch for the duration of the study in order to collect data on sleep, physical activity, heart rate, heart rate variability, and other digital measures available through Apple HealthKit and SensorKit. Participants will also download an app to their personal iPhone which collects additional digital measures, such as activity, environmental light, and wake and sleep patterns. A full list of data collected is available in Supplementary Tables S3, S4. This data is collected throughout the entirety of the 5 week protocol (7 weeks for non-OPTIMA participants). Participants continuing from OPTIMA are asked to continue wearing their Apple Watch during any gap between the end of the OPTIMA protocol and the beginning of the ILIAD protocol (typically < 30 days), such that these participants will have digital phenotyping data available for the same pre-LIFUP period as non-OPTIMA participants.

### 3.5 Affect interview

Participants complete an affect interview prior to the first MRI scan. This is a video-recorded interview in which an experimenter asks seven questions:

How are you feeling today?Did anything happen this week that made you feel angry, stressed, or sad? If yes, describe what happened and how you felt.Did anything happen this week that made you feel good? If yes, describe what happened and how you felt.Is there something you are worrying about? If yes, please describe what is it you're worrying about and how it makes you feel.Is there something good you expect will happen soon that you are looking forward to? If yes, what is it, and how does it make you feel?Have you been planning or working toward a positive future event or experience? If yes, what is it and what have you been doing?Tell me about your happiest memory.

Using sentiment analysis from natural language processing (bidirectional encoder representations from transformers; BERT) (Acheampong et al., 2021) of interview data, we will estimate the probability that the response to each interview question was positive, negative, or neutral in emotional valence. Specifically, we will use the roBERTa-base model, which is trained on 60 million tweets of varying levels of positive and negative sentiment, to estimate the sentiment of each interview question response (Barbieri et al., 2020). Due to the established risks of bias in natural language models trained on social media data, we aim to develop procedures to address potential model bias prior to final analysis of this data (Straw and Callison-Burch, 2020).

### 3.6 TestMyBrain neurocognitive tasks

Neurocognitive tasks are administered remotely through the use of TestMyBrain, a digital platform for cognitive testing. Table 3 lists the name of each task administered, the domain(s) of measurement, and a brief description of each task. A total of seven neurocognitive tasks are administered during pre-scan week (7 days before first scan). At study exit, two neurocognitive tasks are repeated: Multiracial Emotion Identification and Gradual Onset Continuous Performance Test. Tasks can be completed on a participant's smartphone or home computer. All tasks are presented in the fixed order listed in Table 3.

**Table 3 T3:** A description of tasks administered in the TestMyBrain neurocognitive battery.

**Task name**	**Domain**	**Description**
Vocabulary (4 min)	Long-term verbal memory, crystallized cognitive ability, verbal reasoning	A vocabulary word is presented and the user must select 1 of 5 presented words that most closely matches the meaning of the vocabulary word.
Matrix reasoning (7.5 min)	Fluid cognitive ability, nonverbal reasoning	A series of image patterns are presented and the user is asked to select from options, which image will complete the pattern presented.
Multiracial emotion identification (3.5 min)	Face emotion perception, emotion identification	Photographs are presented of individuals expressing either anger, happiness, fear or sadness. The user must select which of the four emotions best describes the face presented.
Choice reaction item (1.5 min)	Processing speed, response selection/inhibition, attention	Three colored boxes are presented, each box contains an arrow that points left or right. Two boxes are the same color, one box is a different color. The user must indicate the direction of the arrow in the box that is a different color than the rest.
Digit symbol matching (2 min)	Processing Speed, visual short term memory	A key that matches numbers with symbols is shown, and the user is asked to match numbers to symbols as they are presented.
Multiple object tracking (5 min)	Visual working memory and visuospatial attention.	A set of target circles moves around the screen, among a larger set of identical distractor circles. The user must remember which circles were designated as targets, and track them throughout their movement alongside distractor circles.
Gradual onset continuous performance test (6 min)	Sustained attention, response inhibition, cognitive control	The user is presented with either a city image or a mountain image at varying intervals. For each image, the user must press a key when a city image appears and not press when a mountain image appears.

### 3.7 Data management and monitoring

#### 3.7.1 Data entry and storage

##### 3.7.1.1 Research Electronic Data Capture

This project utilizes REDCap for data collection and storage. REDCap employs relational database tables within a single MySQL database to store project records and all collected data. Survey data are collected directly from participants through External REDCap utilizing emailed survey links. Collected survey data are automatically synced from the external database to Internal REDCap. Non-survey data such as participant schedules, medication history, and records of in-person data collection are manually input by research staff and stored in Internal REDCap behind secure firewalls. Where third party services are utilized to collect survey data—as is the case for the SAGE Diagnostic Assessment and TestMyBrain Neurocognitive Assessment—External REDCap surveys are used to provide links to the third party site for assessment administration, and the REDCap API is utilized to copy that assessment data into the Internal REDCap database for secure storage within each record.

##### 3.7.1.2 The DGC Study App

The UCLA Depression Grand Challenge Study App (DGC Study App) built by Avicenna Research is installed on participant iPhones and used to collect digital health data. The DGC Study App uses HealthKit and SensorKit APIs for passive measures and deploys ecological momentary assessments (EMAs). The DGC Study App sends collected information to an Amazon Web Services (AWS) environment where EMA data and DGC Study App use activity are stored in a PostGreSQL server and passive sensor data (heart rate, accelerometer, etc.,) are stored in a CassandraDB instance. Data is periodically moved from the AWS server to a UCLA hosted Azure storage environment for storage and analysis.

#### 3.7.2 Data monitoring

Data quality is monitored weekly by the research staff and the program manager in order to ensure data collection occurred as prescribed by the protocol. Bi-weekly progress reports on participant compliance with digital phenotyping data collection are provided by the informatics team. Input and range restrictions for data entry are built into the database whenever possible. Research staff perform quality checks for all records of database entries that are transposed from paper records.

### 3.8 Trial management

#### 3.8.1 Trial registration

This study is registered on clinicaltrials.gov as NCT06285474. It has been approved by the UCLA Institutional Review Board as IRB#22-001323.

#### 3.8.2 Role of study sponsor and multi-institution collaboration

This study was developed by investigators at UCLA as part of the international and multi-institution Wellcome Leap Multi-Channel Psych Program (MCPsych). To facilitate harmonization of collection measures across the program and comparable outcome measures for joint analyses, sites synchronized collection of specific measures across several data collection modalities (i.e., self-report surveys, digital phenotyping, neuroimaging, etc.) in order to have harmonized outcome measures that would be comparable across sites in this consortium. Several protocol changes were initiated due to funding changes during the conduct of the study; the most notable of these changes were the removal of the nucleus accumbens LIFUP group (see Section 3.1) and the transition of the Apple Gathering Task to be outside of the scanner (see Section 3.3).

The trial sponsor is not responsible for any data collection, analysis, or interpretation related to this protocol. However, publications and presentations related to the data collected under the Wellcome Leap contract must receive approval from Wellcome Leap to ensure appropriate protection of intellectual property from other performing sites.

#### 3.8.3 Trial steering committee

The Trial Steering Committee for this protocol comprises the directors of the Depression Grand Challenge, principal and co-investigators of this protocol, as well as other professors, researchers, project scientists, and post-doctoral fellows. This group meets weekly with the research program manager to review study progress, data quality, deviations, protocol amendments, and participant care.

#### 3.8.4 Trial monitoring

A Data Monitoring Committee was not considered as this is a low-risk intervention. Protocol deviations are reported to the relevant centers as directed by the UCLA IRB and Office of Human Research Protection Program. Protocol amendments are communicated to investigative and research operations team members by the program manager through email notifications describing the changes and any impacts to operations. These email notifications include the updated protocol and relevant updated study documents. The clinical trial registry is kept up to date with protocol amendments and trial descriptions as changes are made.

#### 3.8.5 Research operations team

This study is being performed by research operations staff under the UCLA Depression Grand Challenge. The research operations project director provides supervision of study operations and ensures adherence to departmental standards. The project manager is responsible for protocol implementation, management of IRB submissions and study documents, database maintenance, data quality control, data monitoring, and study reporting. The research coordinator is responsible for participant screening, enrollment, and communication, as well as data collection and management. A team of research assessors is responsible for MRI data collection and managing participants in the MRI environment, as well as conducting LIFUP administration. Informatics specialists are an integral part of this protocol, as they are responsible for the management and storage of the multitude of data types, including digital sensing data, survey data, and scan data. Informatics specialists built the study screening website and are responsible for database technical support for this protocol. The study utilizes a third party company, Avicenna (previously Ethica) for app development and hosting to collect data for digital phenotyping and Ecological Momentary Assessment (EMA). This study collects information relating to suicidal ideation, and responses to participants that indicated imminent risk are managed in collaboration with Protocall Services—a third party, 24 h call service—as well as Depression Grand Challenge licensed clinical social workers.

#### 3.8.6 Adverse event monitoring

Adverse events are not explicitly solicited nor investigated under this protocol. However, monitoring for suicidality is conducted 24 h after each LIFUP appointment, as well as 72 h after the final LIFUP appointment. Spontaneously reported events are reported to the investigators in order to assess the probability that they were related to the study intervention. If events are determined to be possibly related, they are reported to the relevant centers as directed by the UCLA IRB and Office of Human Research Protection Program.

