Our study is the first to investigate the effects of LIFUP to the caudate and nucleus accumbens in individuals with anhedonic depression. However, preliminary studies in other populations have demonstrated the safety and feasibility of LIFUP to these regions. A recent study of LIFUP to the caudate in two veterans with post-traumatic headache observed reduced pain levels after several sessions (Yoon et al., 2024). Additionally, a study of long-term repeated administration of LIFUP to the caudate and putamen in non-human primates showed a slight but significant increase in motivation and task accuracy (Munoz et al., 2022). Stimulation of the nucleus accumbens using LIFUP has been found to reduce substance cravings in participants with substance use disorder and to increase connectivity between the nucleus accumbens and medial prefrontal cortex in healthy controls (Mahoney et al., 2023; Peng et al., 2024). Several other studies have also found beneficial effects of LIFUP to other brain regions in depressed participants, namely the subcallosal cingulate cortex and frontotemporal cortex (Reznik et al., 2020; Riis et al., 2024a,b).

Through this double-blinded, sham-controlled study, we hope to gain a better understanding of the feasibility and potential effects of LIFUP stimulation to the caudate head and nucleus accumbens in individuals with anhedonic depression. The study utilizes a wide array of self-report, digital phenotyping, and neuroimaging metrics in order to obtain a maximally comprehensive picture of the potential effects of LIFUP.

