#### 3.2.2 Secondary outcome measures

An additional set of behavioral questionnaires assessing aspects of anhedonia, depression, anxiety, and general mental wellbeing are collected at baseline and at the end of the study. A list of assessments used for this study is available in Table 2, alongside descriptions of each assessment. Two secondary outcome assessments, The Modified SITBI-R + CSSRS-SR (MSC-SR)^4^ and the Eudaimonic Wellbeing Questionnaire,^5^ were developed by the study team for the purposes of this study; further information regarding the development of these assessments is available in the Supplementary Methods S2, S3. The schedule of administration for these measures is available in Supplementary Table S2, and full assessments are available in the Supplementary Forms.

**Table 2 T2:** A list of the self-report questionnaires, neurocognitive tests, and interviews administered as part of the ILIAD protocol and descriptions of each measure.

**Assessment**	**Assessment type**	**Description**
Ecological Momentary Assessment (EMA)	Primary outcome	Self-reported current mood, environment, experiences, and anhedonic state
Positive Valence Systems Scale (PVSS-21)	Primary outcome	Self-reported index of anhedonia and reward processing, 21 items
Patient Health Questionnaire - modified (PHQ-14)	Primary outcome	Self-reported depression severity, 14 items
Patient Health Questionnaire (PHQ-9)	Secondary outcome/adverse event monitoring	Self-reported depression severity, 9 items
Quick Inventory of Depressive Symptoms (QIDS-SR15)	Secondary outcome	Self-reported depression symptoms, 15-items
Brief Irritability Test (BITe)	Secondary outcome	Self-report irritability measure, 5-items
Modified SITBI-R+CSSRS-SR (MSC-SR)	Secondary outcome	Self-report of suicidal ideation and behavior
Generalized Anxiety Disorder Questionnaire (GAD-7)	Secondary Outcome	Self-reported anxiety symptoms, 7-items
Work and Social Adjustment Scale (WSAS)	Secondary outcome	Self-reported functional impairment of current symptoms in work/school, social life, and family life
World Health Organization (WHO)-5 Wellbeing Index	Secondary outcome	Self-reported current mental wellbeing
Pittsburgh Sleep Quality Index (PSQI)	Secondary outcome	Self-reported recent sleep quality
Snaith-Hamilton Pleasure Scale (SHAPS)	Secondary outcome	Self-reported hedonic experience or positive valence
Apathy Motivation Index (AMI)	Secondary outcome	Self-report index of apathy and motivation

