This study is also one of the first studies to investigate the effects of multiple sessions of deep brain LIFUP on depressive and anhedonic symptoms; previous multi-session LIFUP studies in clinical populations have found significant impacts on anxiety symptoms (Mahdavi et al., 2023), autism spectrum disorder symptoms (Cheung et al., 2023), and worry symptoms (Reznik et al., 2020). Furthermore, a single, 40-min session of LIFUP to the subcallosal cingulate cortex was recently found to reduce depressive symptoms in individuals with treatment resistant depression (Riis et al., 2024a,b). However, none of these previous studies included longitudinal neuroimaging measures or continuous physiological monitoring. As a result, this study is a critical step forward in the investigation of the potential neurological and physiological effects of multi-session deep brain LIFUP. This is especially important given that most other non-invasive brain stimulation techniques used in psychiatric applications, such as transcranial magnetic stimulation (TMS) and transcranial direct current stimulation (TDCS) require multiple sessions for optimal treatment response (Li et al., 2022; Hutton et al., 2023). While this study still does not reach the 10+ sessions typically used in TMS and TDCS applications, a demonstration of the feasibility and safety of multi-session LIFUP through this protocol would provide support for the investigation of more intensive LIFUP protocols in future studies.

A notable limitation of this study protocol is the timeline variability across participants. The time course of LIFUP effects after multiple consecutive sessions has not yet been investigated and is therefore unknown. Thus, while the 3–14 day window between the last LIFUP session and the post-LIFUP MRI is necessary for the logistical feasibility of the study, there is a chance that the effects observed in the neuroimaging data for each participant may be strongly impacted or even rendered undetectable by the relative timing of the post-LIFUP MRI. This is a critical confound that will need to be controlled for in analyses; however, this range of timepoints may also facilitate investigation of the time course of post-LIFUP changes in neurological function.

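### Physical and neurological adverse events are recorded only if volunteered, so the trial cannot supply the demonstration of safety that the Discussion says would support more intensive LIFUP

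*Protocol article*

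**What the plan says.** Section 3.8.6 sets the rule on harms: "Adverse events are not explicitly solicited nor investigated under this protocol". It then names one exception, namely that "monitoring for suicidality is conducted 24 h after each LIFUP appointment, as well as 72 h after the final LIFUP appointment". For everything else, "Spontaneously reported events are reported to the investigators in order to assess the probability that they were related to the study intervention", and those judged possibly related are reported onward to the relevant centers. Table 2 (Section 3.2.2) gives the PHQ-9 the label "Secondary outcome/adverse event monitoring", and Section 4.1 places it one day after each LIFUP session.

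The Introduction states the purpose without naming safety: "we hope to gain a better understanding of the feasibility and potential effects of LIFUP stimulation to the caudate head and nucleus accumbens". Section 5 goes further: "a demonstration of the feasibility and safety of multi-session LIFUP through this protocol would provide support for the investigation of more intensive LIFUP protocols".

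The Abstract calls this the first study of LIFUP to these targets in depressed subjects. The Introduction takes its earlier safety evidence for these regions from other populations. Section 2.1 counts as evaluable only those who complete all three sessions, both scans and at least one later outcome measure.

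**The concern.** Section 5 ties a possible safety conclusion to this trial's own data and gives it a use: support for more intensive protocols. Section 3.8.6 removes most of the data that such a conclusion needs. If nobody is asked about headache, scalp symptoms or neurological symptoms, a short list of reports may mean few events or few questions, and the data cannot tell these apart.

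The sham arm would normally help, because the same questions under blinding give a controlled comparison. For physical and neurological events no such comparison is described in Section 4. A separate analysis plan could not supply one either, because the events are not systematically collected.

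The evaluable definition adds a smaller risk. Section 3.1.2 lets participants stop a session for discomfort. Someone who left the study for that reason would fall outside the evaluable set, so a harms summary restricted to that set would miss the people most relevant to it.

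**Working it through.** The article states no adverse event rate or safety target, so there is no figure to reproduce. The main check compares what is ascertained with what is to be concluded.

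**What is ascertained**
- Actively, at fixed times: suicidality after each session; PHQ-9 one day after each session; weekly PHQ-14 and PVSS-21; EMA; scales for anxiety, irritability, sleep and suicidal ideation at baseline and study end.
- Also repeated: the T1 structural scan after LIFUP (Section 3.3) and two neurocognitive tasks at exit (Section 3.6).
- Only if volunteered: physical and neurological symptoms, and any other event.

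**What is to be concluded** (Section 5): safety of multi-session LIFUP, without restriction to mood or suicidality. The conclusion is wider than the ascertainment.

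**Scale, under stated assumptions**

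The numbers of active participants are assumptions. If the minimum of 40 evaluable participants includes the six active accumbens participants and the other 34 split equally, there are 17 active caudate, and 17 + 6 = 23 active in total. If instead 40 are split equally, there are 20 active, and 26 with the six accumbens participants added on top.

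With zero events in n participants and complete capture, the exact one-sided 95% upper bound solves (1 − p)^n = 0.05, so p = 1 − 0.05^(1/n):
- n = 17: 16.2%
- n = 20: 13.9%
- n = 23: 12.2%
- n = 26: 10.9%

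A harms denominator should be everyone treated, which may be larger. If 100 were enrolled and 50 received active treatment (assumption), the bound would be 5.8%.

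If only a share s of events is reported, zero *recorded* events gives (1 − ps)^n = 0.05, so the bound becomes [1 − 0.05^(1/n)]/s. The documents give no value for s. Assumed values show the direction:

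| Assumed s | n = 20 | n = 26 |
|---|---|---|
| 1.0 | 13.9% | 10.9% |
| 0.7 | 19.9% | 15.5% |
| 0.5 | 27.8% | 21.8% |
| 0.3 | 46.4% | 36.3% |

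The chance of recording at least one case of an event with a true rate of 10% is 1 − (1 − 0.10s)^n. For n = 20 it is 0.88 at s = 1, 0.64 at s = 0.5 and 0.46 at s = 0.3.

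Because s is unknown under the stated rule, none of the rows below the first can be chosen, and no valid upper bound can be reported.

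**The case against.** The strongest reply is that the trial never sets out to establish safety. The Introduction names feasibility and potential effects, no safety outcome is listed, and the sentence in Section 5 is conditional. This stands as far as it goes. A reader might infer that demonstrating safety is an aim of the trial, and the documents do not support that. It does not remove the conflict, because the condition in Section 5 is one that data collected under Section 3.8.6 cannot meet for most kinds of harm.

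A reader might also infer that nothing but spontaneous reports is captured, or that every comparison of harms between arms is lost. Neither is right. Suicidality and worsening of mood, anxiety, irritability or sleep are measured on a schedule that does not depend on arm, under blinding, and can be compared. Nor does Section 3.8.6 say that unrelated events go unrecorded: the relatedness judgement governs onward reporting.

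A further tempting step is to add the absence of independent oversight: "A Data Monitoring Committee was not considered as this is a low-risk intervention". The article gives its reason, and a committee would not change how events are found, so this is not part of the point.

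Two practical objections stand. The trial is under way and all six active accumbens participants have been treated, so solicited data cannot cover everyone. And even full solicitation leaves a bound above 10% at the minimum sample size, so a checklist makes the harms data interpretable but does not by itself demonstrate safety.

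**Conclusion.** The point holds in a limited form. Sections 3.8.6 and 5 of the protocol article must be reconciled: absence of volunteered reports cannot support a general statement on the safety of multi-session LIFUP, although a narrower statement on suicidality and the other measured scales is possible. The article makes an affirmative statement that events are not solicited, so this is not a detail left to a fuller document.

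On size, a bound of about 11% to 16% after zero events is the best case for 17 to 26 active participants. It rests on assumed splits around the minimum of 40 evaluable and on complete capture. Treating more participants would lower it, and under-reporting would raise it by an amount that the design leaves unknown. The primary efficacy analyses are not affected. What is at stake is the harms conclusion and its proposed use.

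**What to change.** **Collection.** For remaining participants, amend Section 3.8.6 to add a short fixed adverse event checklist with identical questions in both arms. Ask it at each LIFUP visit, at the existing 24 h and 72 h monitoring points, and at scan 2. Record every event before any judgement of relatedness.

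**Reporting.** Tabulate events by assigned arm for everyone who received any session, not only evaluable completers. Show participants treated before the change separately, labelled as unsolicited ascertainment; these include the six active accumbens participants. Do not pool the two periods into one rate.

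**Wording.** In any case, limit the Section 5 sentence to feasibility and to the harms actually ascertained. If the checklist is not added, take the word safety out of it.

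**Cost.** One protocol amendment, one REDCap form, a little time at scheduled points and more minor events to log. If the 24 h and 72 h monitoring is by survey rather than by staff contact, the checklist would be delivered as a survey too. Ascertainment will be mixed across the trial, and that limitation has to be stated with the results.
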